### Compliance management

2.8

Given a home-based setup, it is important to promote adherence and conduct compliance management. To promote adherence to the program, a self-reported sports diary and a sports bracelet will be given to each participant to provide daily visual feedback and empower responsibility for their daily and weekly goals. Additionally, following a demonstration of the functional resistance exercises at their initial assessment, participants are provided with written and pictorial instructions, as well as a video of all of the exercises. All subjects are pulled into a WeChat group, each exercise record is uploaded to the group, and the “social comparison theory” is adopted to promote patients to complete the exercise.^[22]^ In addition to encouraging patients to complete exercise and punch on time at WeChat Group, the experimenter will conduct weekly telephone surveys to encourage patients to complete family exercise diaries. Any problem can be reported, such as pain or discomfort, to adjust the exercise prescription appropriately. The patients are encouraged during telephone counseling, and their efforts are praised.

### Satisfaction survey

2.9

Before the patient is discharged from the hospital after the kidney transplantation, the satisfaction survey will be completed (Table 5), and the patient is asked to make suggestions on the family exercise program.

**Table 5 T5:** Satisfaction survey.

Satisfaction survey	
Satisfaction with home exercise pre-rehabilitation	□Very dissatisfied □Dissatisfied □Generally □satisfied □ very satisfied.
Does home exercise pre-rehabilitation help you?	□Very dissatisfied □Dissatisfied □Generally □satisfied □ very satisfied.
The degree of difficulty of home exercise pre-rehabilitation	□Very difficult □difficult □Generally □Easy □Very easy

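### The helpfulness item in the satisfaction survey carries satisfaction answer options, so its answers cannot be clearly reported as perceived helpfulness

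*Protocol article*

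**What the plan says.** Section 2.9 of the protocol article places one survey at the end of the transplant admission: "the satisfaction survey will be completed (Table 5), and the patient is asked to make suggestions on the family exercise program". Table 5 prints the form. It has three closed items, each with five ordered options.

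- Item 1 is "Satisfaction with home exercise pre-rehabilitation", with the options "Very dissatisfied □Dissatisfied □Generally □satisfied □ very satisfied".
- Item 2 is "Does home exercise pre-rehabilitation help you", with the same five options as item 1.
- Item 3 concerns how difficult the programme was, with the options "Very difficult □difficult □Generally □Easy □Very easy".

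The survey is not among the outcomes in Sections 2.6.1 and 2.6.2, has no row in the schedule in Table 4, and is not named in Section 2.11 on statistical analysis.

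**The concern.** Item 2 asks one thing and its options answer another. The stem is about benefit: did the programme help? The options are degrees of satisfaction. No option says that it helped a lot, a little or not at all.

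Satisfaction and perceived benefit can part company. A patient may like the coaching and weekly calls yet feel no stronger for them. Another may find the exercises tiresome and still judge them useful. With the same scale under both questions, the form does little to separate the two, and a share of satisfied answers to item 2 could be written up as the share of patients who found the programme helpful.

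The trial is meant to show whether a randomised trial is possible and how it should be designed. Whether patients think a home programme did them any good is useful for that purpose. The survey is given once per patient, so the plan provides no later occasion to ask again.

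**Working it through.** No formula applies and the plan states no figure to reproduce. The check sets each stem in Table 5 beside its options and then looks for anything elsewhere in the article that would settle how item 2 is to be read.

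**Step 1: stem against options.**

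| Item | What the stem asks about | What the options grade | Match |
|---|---|---|---|
| 1 | Satisfaction | Satisfaction, five points | Yes |
| 2 | Whether the programme helps | Satisfaction, five points, word for word as item 1 | No |
| 3 | Difficulty | Difficulty, five points | Yes |

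One item in three does not match.

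**Step 2: could this be a fault in reading the table?** Unlikely. The table is otherwise intact, with three stems and three complete rows of options. Item 3 has a different scale that suits its stem, so the form was not built on one generic scale for all items. The pattern looks more like a row of options repeated by mistake.

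**Step 3: does another section resolve it?** No.

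- The outcome sections (2.6.1 and 2.6.2) do not mention the survey.
- The analysis section (2.11) does not say how any survey item is scored or read.
- SF-36 and HADS measure health status and mood. They do not ask for the patient's opinion of the programme.
- The weekly telephone contacts in Section 2.8 serve encouragement and the reporting of problems.
- Section 2.7 records agreement to take part, reasons for declining, and completion of the exercise plan. These are not ratings of benefit.

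Table 5 is therefore the only structured rating of the programme by patients in the article. Item 2 is the only closed question on perceived benefit.

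**Step 4: how many answers are affected?** The planned sample is 47. The survey is completed before discharge after transplantation, so only participants who are transplanted and reach that point can answer it. Hence 47 is an upper bound. The article gives no expected number transplanted during the study, so no closer figure can be derived.

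**Step 5: what can still be read from item 2?** The stem does ask about help, and the options run in order from negative to positive. An answer therefore carries some direction. What it lacks is a clear meaning: the same tick could come from a patient rating benefit and from one rating satisfaction again, and nothing on the form separates them.

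**The case against.** The case on the other side has five parts.

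**The item is not empty.** A reader might infer that perceived benefit cannot be measured at all, or that every answer to item 2 is worthless. The article does not support that. The stem is plain, the scale is ordered, and some patients will answer with benefit in mind. The supportable word is ambiguous. A reader might also infer that item 2 merely repeats item 1. It does not: the stems differ, and only the answer scale is shared. This objection stands and limits the point.

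**The survey is peripheral.** It is not a listed outcome, and no test or sample-size input depends on it. The Discussion names recruitment, dropout, transplantation or death during the study, and programme completion as what the trial should clarify. Perceived helpfulness is not named. This stands, and it is why the impact is minor.

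**Other feedback exists.** Patients are asked for suggestions in the same sentence that introduces the survey, problems can be raised in the weekly calls, and items 1 and 3 are sound. So acceptability information is not lost. These channels do not, however, supply a rating of benefit on a common scale.

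**Misreporting is not planned.** The article sets no reporting rule for the survey, so it does not say that item 2 will be presented as helpfulness. Nor does it propose a combined score, so there is no need to ask for the items to be kept apart in reporting. Both observations are right. The risk lies in what a later analyst would naturally do with an item whose stem says help.

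**The cause may be a slip in the article.** This is an English-language account of a single centre in China, and the form handed to patients is not shown. The mismatch could have arisen in copying or translation. That cannot be excluded, so the first step has to be to look at the form in use. It does not make the printed item sound.

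**Conclusion.** The point holds in a limited form. As printed, the options for item 2 of Table 5 do not match its question, so the answers may be read as a second satisfaction rating and cannot be clearly reported as perceived helpfulness.

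The size is small. One of three closed items is affected, for no more than 47 respondents, in a questionnaire outside the primary and secondary outcomes. No sample-size, efficacy or safety conclusion is touched. It deserves correction because this is the only place where patients grade the programme itself, in a trial run to inform the design of a larger one, and because correction is easy.

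The conclusion rests on one assumption: that the form given to patients carries the options printed in Table 5. If that form already has a helpfulness scale, only the published table needs correcting.

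**What to change.** 1. Check the form that patients are given, in the language in which they receive it.
2. If it has the same mismatch, replace the options of item 2 with a five-point helpfulness scale, for example: not at all helpful, slightly helpful, moderately helpful, helpful, very helpful. Items 1 and 3 stay as they are.
3. If the form is already correct, amend Table 5 to agree with it.
4. If some surveys have been completed on the old options, report those item 2 answers as satisfaction-scaled, state how many there are, and do not pool them with answers to the corrected item.

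The cost is one row on a form, plus any version control or ethics notification that the centre requires for a revised questionnaire. Visits, sample size, planned tests and patient care are unaffected. The article does not say whether any survey has been completed. If some have, the added cost is a separate line in the report and fewer answers on the corrected scale.

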### Sample size calculation

2.10

According to existing literature (Manfredini Fabio, Mallamaci Francesca, D’Arrigo Graziella et al. Exercise in Patients on Dialysis: A Multicenter, Randomized Clinical Trial.[J]. J Am Soc Nephrol, 2017, 28: 1259–1268), G-power3.1 software will be used to calculate the sample size. By paired-samples *t* test, the effect size = 0.37, α = 0.05, and power size = 0.80, and the calculated sample size is 47.

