**Methodology::**

The proposed feasibility trial will be a single-arm, single-center study. A total of 47 ESRD patients awaiting kidney transplantation will be selected as subjects to undergo personalized family exercise pre-rehabilitation, including aerobic exercise, functional resistance exercise, and flexibility training. Briefly, a 6-minute walking test (6MWT), 4-meter gait speed, grip strength, and sit-to-stand test will be used as the main outcome indicators. The effect of family exercise pre-rehabilitation on the optimization of body function in ESRD patients undergoing kidney transplantation will be assessed. The days of hospitalization after kidney transplantation, postoperative complications, health survey (the Short Form Health Survey, SF-36), and the Hospital Anxiety and Depression Scale (HADS) will be used as secondary outcome indicators to evaluate the improvement of quality of life, psychological function, and postoperative rehabilitation of patients after kidney transplantation. These indexes will be collected before and after intervention (baseline and before kidney transplantation), before discharge (after kidney transplantation), and 1 month after discharge.

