### Statistical analysis

2.11

SPSS24.0 statistical software and Office Excel 2016 will be used to analyze the test data. The quantitative data will be tested by the Kolmogorov–Smirnov test to determine whether they are following a normal distribution. Quantitative data: if the comparison before and after the intervention follows the normal distribution, the paired sample *t* test will be used; if it does not meet the normal distribution, the non-parametric test Wilcoxon symbolic rank test will be used for analysis. The results are expressed as mean ± standard deviation (
$\bar{X}\pm S$
). The postoperative hospitalization days, postoperative complications, postoperative drainage, and extubation are compared with the previous data in the hospital. If the data satisfies normal distribution, an independent sample *t* test will be used; otherwise, the Mann–Whitney *U* test is used for analysis, and the results are all expressed as mean ± standard deviation (
$\bar{X}\pm S$
). The qualitative data will be analyzed by chi-square test (χ^2^ test), and the results are expressed as a percentage (%). The level of significance is *P* < .05.

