This Phase I trial is essential to understand potential recruitment rates, dropout rates, patients who receive transplants or die during the study, and the completion rate of this program to accurately motivate participants for future RCTs.

Collectively, this trial is a practical, single-center, single-arm, exploratory clinical trial. We plan to show that ERAS-based home exercise pre-rehabilitation will reduce the adverse effects of frailty, cardiopulmonary dysfunction, and psychological dysfunction on the prognosis of renal transplantation.

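### The sample size of 47 gives 80% power only with a one-sided test; at the usual two-sided P < .05 power is about 70%, and lower after any loss to reassessment

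*Protocol article*

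**What the plan says.** Section 2.10 takes an effect size from a published exercise trial in dialysis patients and says that "G-power3.1 software will be used to calculate the sample size". The inputs and the result, for a paired t test, are: "the effect size = 0.37, α = 0.05, and power size = 0.80, and the calculated sample size is 47". It does not say whether the test has one tail or two.

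Section 2.11 compares values before and after the intervention with a paired t test, or the Wilcoxon signed rank test if the data are not normal. It also names the independent-samples t, Mann–Whitney and chi-square tests for other comparisons. One criterion covers them all: "The level of significance is *P* < .05".

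The abstract makes the calculated figure the enrolment figure: "A total of 47 ESRD patients awaiting kidney transplantation will be selected as subjects". Under section 2.5, the second functional assessment takes place when the patient comes back to hospital for the transplant. The Discussion lists what the trial is meant to learn: "This Phase I trial is essential to understand potential recruitment rates, dropout rates, patients who receive transplants or die during the study".

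**The concern.** With a standardised paired change of 0.37, 5% significance and 80% power, a two-sided paired t test needs clearly more than 47 pairs. The stated figure therefore looks like the one-tailed answer, while the analysis section reads as ordinary two-sided testing. If so, the sample size and the analysis rest on different tests, and the 80% does not describe the analysis a reader would expect.

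A second matter adds to this. The calculation counts complete pairs, but the same 47 is the number enrolled. A patient who is not called for transplantation, dies or withdraws supplies no second measurement.

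The functional measures are the primary outcomes and are tested formally. A non-significant result would be read against a claimed 20% chance of missing the assumed effect. On the two-sided reading that chance is 30% before any loss.

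**Working it through.** **Inputs.** From section 2.10: paired t test, effect size d = 0.37 (mean paired change divided by its standard deviation), α = 0.05, target power 0.80, stated n = 47. From section 2.11: P < .05, sidedness not given.

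**Formula.** With n complete pairs, the paired t statistic follows a noncentral t distribution with n − 1 degrees of freedom and noncentrality λ = d·√n. Power is the probability that it exceeds the critical value t(1 − α, n − 1) for a one-sided test, or lies beyond ± t(1 − α/2, n − 1) for a two-sided test.

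**Step 1: reproduce the stated 47.** At n = 47, λ = 0.37 × √47 = 2.537 with 46 degrees of freedom. The one-sided critical value at 0.05 is 1.679, which gives power 0.803. At n = 46 the one-sided power is 0.796. The smallest n that reaches 80% is therefore 47, an exact match.

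**Step 2: the same inputs, two-sided.** At n = 47 the critical value is 2.013 and power is 0.700. Power is 0.798 at n = 59 and 0.805 at n = 60, so 60 complete pairs are needed.

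**Step 3: normal approximation as a check.** n ≈ ((z for α + z for power) / d)².
- One-sided: ((1.645 + 0.842) / 0.37)² = 45.2
- Two-sided: ((1.960 + 0.842) / 0.37)² = 57.3

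Both fall slightly below the exact answers, as expected, and the gap between the tests is the same.

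**Step 4: could rounding explain it?** Effect sizes that round to 0.37 run from 0.365 to just under 0.375. Over that range the two-sided requirement is 61 down to 58 pairs, so rounding does not lead to 47.

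**Step 5: the effect 47 pairs can detect.** Solving for d at 80% two-sided power gives 0.417 with 47 pairs and 0.467 with 38.

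**Step 6: loss to reassessment.** The article gives no rate, so the rates below are assumptions. All powers are for d = 0.37.

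| Assumed loss | Complete pairs | Two-sided power | One-sided power |
|---|---|---|---|
| none | 47 | 70.0% | 80.3% |
| about 10% | 42 | 65% | 76% |
| about 20% | 38 | 60% | 72% |
| about 30% | 33 | 54% | 67% |

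Even under a one-sided test, losing a single pair takes power just below 80% (79.6% with 46).

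**The case against.** The best defence is that nothing was miscalculated. The inputs give exactly 47 under a one-sided test, the hypotheses are directional (the programme is expected to improve function), and the word two-sided does not appear in section 2.10 or 2.11. On this view the defect is an unstated choice, and the 70% exists only once a reader supplies the convention.

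Part of this stands. The 70% is conditional on the usual reading of P < .05, and a one-sided intention cannot be ruled out. But a directional hypothesis does not declare a one-sided test. The analysis section applies one unqualified threshold to all its tests, including chi-square. A one-sided 0.05 test is unusual enough that it has to be stated in advance.

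It can also be said that learning dropout and transplant rates is a purpose of the trial, that patients who pause exercise through illness may continue, and that a condensed article may omit a dropout allowance. That is fair as far as it goes: the loss rates are assumed, and loss is the secondary part of the point. What remains is that the enrolled number equals the required number of complete pairs, which leaves no margin under either test.

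Finally, this is a feasibility study, so power matters less than in a confirmatory trial, and a within-patient calculation would not itself size a later parallel-group trial. Any effect on planning that trial is therefore uncertain. But the article chose to justify its size by formal power on functional primary outcomes, so the figure should be right.

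**Conclusion.** The concern holds. The stated 47 is the one-sided answer. Under the conventional two-sided P < .05, power for an effect size of 0.37 is 70.0% rather than 80%, 60 complete pairs would be needed for 80%, and the effect detectable with 80% power is 0.42. Under assumed losses of about 10% to 30%, two-sided power falls to between 65% and 54%.

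This rests on reading P < .05 as two-sided, because the article is silent, and on taking 0.37 as the standardised paired change; the source of that value was not checked. If a one-sided 0.05 test was meant, 47 is correct for complete data only, and the article needs to say so.

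**What to change.** Keep the enrolment at 47 and restate section 2.10 along these lines: *Two-sided α = 0.05. With 47 complete pairs, power is 70% for a standardised paired change of 0.37 and 80% for a change of 0.42. If 20% of participants have no pre-transplant reassessment, power for 0.37 falls to about 60%.* The 20% should be labelled as an assumption. Section 2.11 should say that tests are two-sided.

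If a one-sided test is really intended, declare it in section 2.10 and apply it in section 2.11. Setting it at one-sided 0.025 would be more usual, but power with 47 pairs is then again 70%. Under one-sided 0.05, the 80% still holds only if all 47 are reassessed, and the text should say this.

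For reference, 80% two-sided power needs 60 complete pairs. The cost is a few sentences in two sections and a less favourable stated power. No extra patients are required and the conduct of the trial does not change.

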### Statistical analysis

2.11

SPSS24.0 statistical software and Office Excel 2016 will be used to analyze the test data. The quantitative data will be tested by the Kolmogorov–Smirnov test to determine whether they are following a normal distribution. Quantitative data: if the comparison before and after the intervention follows the normal distribution, the paired sample *t* test will be used; if it does not meet the normal distribution, the non-parametric test Wilcoxon symbolic rank test will be used for analysis. The results are expressed as mean ± standard deviation (
$\bar{X}\pm S$
). The postoperative hospitalization days, postoperative complications, postoperative drainage, and extubation are compared with the previous data in the hospital. If the data satisfies normal distribution, an independent sample *t* test will be used; otherwise, the Mann–Whitney *U* test is used for analysis, and the results are all expressed as mean ± standard deviation (
$\bar{X}\pm S$
). The qualitative data will be analyzed by chi-square test (χ^2^ test), and the results are expressed as a percentage (%). The level of significance is *P* < .05.

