## Materials and methods

2

The proposed feasibility trial is a single-arm, single-center study of an ERAS-based home exercise pre-rehabilitation for patients listed for kidney transplantation. ESRD patients awaiting kidney transplantation will be selected as subjects to undergo personalized family exercise pre-rehabilitation, including aerobic exercise, functional resistance exercise, and flexibility training. Briefly, a 6-minute walking test (6MWT), 4-meter gait speed, grip strength, and sit-to-stand test will be used as the main outcome indicators. The effect of family exercise pre-rehabilitation on the optimization of body function in ESRD patients undergoing kidney transplantation will be assessed. The days of hospitalization after kidney transplantation, postoperative complications, health survey (the Short Form Health Survey, SF-36), and the Hospital Anxiety and Depression Scale (HADS) will be used as secondary outcome indicators to evaluate the improvement of quality of life, psychological function, and postoperative rehabilitation of patients after kidney transplantation. These indexes will be collected before and after intervention (baseline and before kidney transplantation), before discharge (after kidney transplantation), and 1 month after discharge. In addition, age, sex, race, type of occupation, marital status, education, body mass index (BMI), duration of dialysis, causes of ESRD, and types of renal replacement therapy should be recorded. A study schema is provided in Figure 1.

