### Inclusion criteria

2.3

The inclusion criteria will be set as follows:

1.ESRD patients are estimated to undergo kidney transplantation in more than 12 weeks, and the first kidney transplant is on the waiting list of the deceased donor in the Second Affiliated Hospital of Hainan Medical University;2.the age is 18 to 60 years old; and3.patients volunteer and sign the informed consent form.

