### Exclusion criteria

2.4

The following patients will be excluded from the study:

1.patients with unstable angina pectoris, new arrhythmia, recent myocardial infarction, or unstable cardiovascular events;2.patients with a recent cerebrovascular accident, or a modified RANKIN score (Modified Rankin Scale, mRS) ≥ 3; and3.those who cannot participate in the exercise due to other serious diseases.

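### Postoperative outcomes are tested, unadjusted, against an undefined historical group, so case mix and calendar time are confounded with pre-rehabilitation

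*Protocol article*

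**What the plan says.** The design has no concurrent control. Section 2 (Materials and methods) states: "The proposed feasibility trial is a single-arm, single-center study of an ERAS-based home exercise pre-rehabilitation for patients listed for kidney transplantation".

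For the postoperative outcomes, section 2.11 (Statistical analysis) brings in an external comparator: "The postoperative hospitalization days, postoperative complications, postoperative drainage, and extubation are compared with the previous data in the hospital". Quantitative outcomes go to an independent-samples t test or, if not normal, to Mann–Whitney U. For the rest, "The qualitative data will be analyzed by chi-square test". The significance level is P < .05. The article does not give the period, source, number or eligibility of the historical patients, and it mentions no covariate model, matching or weighting.

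The participants, by contrast, are clearly restricted:

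- Section 2.3 requires age 18 to 60, informed consent as a volunteer, an expected wait of more than 12 weeks, and that "the first kidney transplant is on the waiting list of the deceased donor".
- Section 2.4 excludes unstable cardiac disease, recent cerebrovascular accident or a modified Rankin score of 3 or more, and "those who cannot participate in the exercise due to other serious diseases".

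Sections 2 and 2.7 record age, sex, BMI, dialysis history, type of renal replacement therapy and cause of ESRD. Section 2.11 uses none of them in this comparison.

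**The concern.** Two groups that differ before any exercise takes place are compared as if they differed only in pre-rehabilitation. Two sources of difference can be seen in the article itself.

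- **Case mix.** Participants pass age, transplant-type, cardiac, cerebrovascular and fitness filters and agree to take part. No such filter is stated for the comparator.
- **Calendar time.** The hospital has been qualified for kidney transplantation since 2010 (section 2.1), so earlier records could reach back about a decade. The Introduction and Discussion both describe surgical technique as steadily maturing, and the Introduction adds that perioperative management is being optimised.

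Stay, complications, drainage and extubation have no pre-intervention value, so the paired tests used elsewhere cannot address them. The historical comparison is the only test they receive. The Introduction nevertheless hypothesises fewer complications and better transplant results, and the Discussion says the trial plans to show a prognostic benefit. A P value below .05 from this comparison could be read as support for that claim and carried into the design of the later randomised trial.

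**Working it through.** **The plan's own figure.** Section 2.10 gives N = 47 from a paired t test with effect size 0.37, α = 0.05 and power 0.80. The noncentral t distribution reproduces 47 with a one-sided α (power 0.803). A two-sided α would need 60. Either way, this figure sizes the before–after comparison. The article gives no sizing for the historical comparison, so 47 is used below only as the size of the trial group.

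**Inputs**

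- Trial group: n = 47 (section 2.10), assuming every participant is transplanted and contributes data.
- Historical group: m = 150, about one year's volume (section 2.1), or m = 300, about two years. Both are assumptions, since no period is stated.
- Test: independent t test, α = 0.05, taken as two-sided. Section 2.11 does not state sidedness.
- Treatment effect: zero.
- Shift from case mix and calendar time: b = 0.1, 0.2 or 0.3 SD. This is an assumption, since the documents give no value.

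**Formula.** The test statistic follows a noncentral t with n + m − 2 degrees of freedom and noncentrality b / √(1/n + 1/m). The rejection probability is the mass beyond ± the 97.5% point of the central t.

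- m = 150: √(1/47 + 1/150) = 0.1672, 195 degrees of freedom, critical value 1.972.
- m = 300: √(1/47 + 1/300) = 0.1569, 345 degrees of freedom, critical value 1.967.

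| Assumed shift b | Noncentrality, m = 150 | Rejects, m = 150 | Noncentrality, m = 300 | Rejects, m = 300 |
|---|---|---|---|---|
| 0 | 0 | 5% | 0 | 5% |
| 0.1 SD | 0.60 | 9% | 0.64 | 10% |
| 0.2 SD | 1.20 | 22% | 1.27 | 25% |
| 0.3 SD | 1.79 | 43% | 1.91 | 48% |

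A larger historical pool makes the standard error smaller but leaves the shift unchanged, so false positives become more frequent.

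**Complications.** The documents give no rate, so 5% and 10% are assumed. The expected count among 47 participants is 47 × 0.05 = 2.35 or 47 × 0.10 = 4.7. Full enumeration of the uncorrected chi-square test with equal true rates gives a type I error of 4.1% (5% rate) and 5.0% (10% rate) for 47 vs 150, and 4.1% and 4.7% for 47 vs 300. The test keeps its level when the groups are comparable. Total events for 47 + 150 patients would be 197 × 0.05 ≈ 10 or 197 × 0.10 ≈ 20, which limits how many covariates a complication model can carry.

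**The case against.** The strongest defence is that this is a condensed article about a feasibility trial. The outcomes are secondary, the Discussion calls the trial exploratory, and a randomised trial is to follow. The period and eligibility of a historical cohort commonly sit in the full protocol or analysis plan, so their absence here is not in itself a fault. That is fair and it limits the point. It does not remove it: the article fixes the tests, those tests are unadjusted, and the exploratory label sits beside a P < .05 threshold and a stated plan to show benefit.

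A reader might also infer more than the article supports:

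- **That the comparator is unselected.** Section 2.11 does not say so. It states no selection either way, so the group is undefined.
- **That a significant difference is likely even if the programme does nothing.** Every rejection rate in the table is below 50%, and all rest on assumed shifts. The supported statement is that the false-positive rate can rise well above 5%.
- **That the bias must favour the trial group.** Excluding unstable or unfit patients and improving care over time make that plausible. No favourable direction is documented for limiting entry to deceased-donor recipients with a long expected wait. Surviving the wait does not separate the groups either, because every historical recipient also reached transplant.
- **That chi-square is unreliable because expected counts fall below 5.** The enumeration shows that its type I error stays at or slightly below 5%.
- **That this comparison carries every claim about recovery.** SF-36 and HADS are also used to assess quality of life and psychological function, with follow-up at 1 month. It is the only test of the four outcomes listed in section 2.11.

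**Conclusion.** The concern holds. Followed as written, section 2.11 cannot separate an effect of pre-rehabilitation from differences in case mix and calendar time for stay, complications, drainage and extubation. The lack of adjustment is a stated choice of test and not merely missing detail.

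The size of the bias is unknown. The rejection rates of 9% to 43% (150 controls) and 10% to 48% (300 controls) illustrate what shifts of 0.1 to 0.3 SD would do to a two-sided 5% t test with no treatment effect and all 47 participants analysed. They are not estimates for this hospital. Because the outcomes are secondary and the trial precedes a randomised one, this should be corrected but does not undermine the feasibility aims.

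**What to change.** Change section 2.11 as follows.

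1. Define the comparator as consecutive patients from a stated recent period at the same hospital who meet the trial criteria that records can show: age 18 to 60, first deceased-donor transplant, and the same cardiac and cerebrovascular exclusions.
2. For continuous outcomes, adjust by regression or propensity weighting for age, sex, BMI, dialysis duration and type, and cause of ESRD. The trial already collects these in participants.
3. For complications, use weighting or a very small penalised model, or report them descriptively. About 10 to 20 events at the assumed rates, and fewer once the comparator is restricted, will not support the full covariate list.
4. Report differences with 95% confidence intervals, and state that the comparison is non-randomised and exploratory and cannot by itself support a claim of reduced complications.

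The cost is some chart abstraction and a smaller comparator group. Volunteer effects and part of the calendar-time difference will remain, which is why the statement in step 4 is needed even after adjustment.
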